#### EOTA + Traction Group

Subjects in the EOTA + traction group will include the EOTA components described above. Mechanical lumbar traction will be applied using a 3D ActiveTrac traction table (Chattanooga Group, Hixson, TN), a motorized, split-table, traction device with a surface that can be adjusted in 3 dimensions (flexion/extension, rotation, and side bending). Subjects will be positioned prone with the table in a neutral position in all planes. If this position causes peripheralization or an intolerable increase in symptoms, the table will be adjusted using flexion or side-bending to promote centralization of symptoms and subject comfort as needed.

Static traction will be applied for a maximum of 12 minutes total, which consists of 10 minutes at the desired intensity, plus 1-minute ramp-up and ramp-down times. The intensity of the pull will be 40-60% of the subject's body weight, adjusted based on the subject's tolerance and symptom response. After 3 minutes of traction, if the table was initially positioned in flexion or side bending, the table will be repositioned as tolerated to achieve a neutral lumbar posture. "Tolerance" will be defined as the ability to achieve a neutral posture (or as close as possible) without peripheralization of symptoms or significant increase in LBP. If the table was initially positioned using both flexion and side-bending, the table will be repositioned first to correct the side-bending accommodation, and then to correct the flexion accommodation. It may not be possible to achieve the goal of a neutral posture during each session, but the goal will be to be as close to neutral posture as tolerated by the subject each session.

At the end of traction treatment, the subject will lie still for 2 minutes prone. For subjects who end their traction treatment in a flat (neutral) position, additional extension positioning will be attempted as follows: the table will be positioned in up to 10 (of extension as tolerated, and the patients will lie still in this position for an additional 2 minutes. For patients who did not end the traction treatment in a flat (neutral) position, no extension positioning will be attempted. At the conclusion of the traction treatment, the subject will be assisted to stand and walk. Flexion, side bending, and sitting positions are to be minimized as much as possible following the traction treatment. If tolerated, the subject will be instructed to perform the same home program of extension-oriented exercises as described in the EOTA group. The mobilization component of the EOTA will be added in the 3^rd ^week for patients in the EOTA plus traction group.

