**Methods/Design:**

The study will recruit 120 patients with low back pain and signs of nerve root irritation. Patients will be randomized to receive an extension-oriented treatment approach, with or without the addition of mechanical traction. Randomization will be stratified based on the presence of the pre-defined sub-grouping criteria. All patients will receive 12 physical therapy treatment sessions over 6 weeks. Follow-up assessments will occur after 6 weeks, 6 months, and 1 year. The primary outcome will be disability measured with a modified Oswestry questionnaire. Secondary outcomes will include self-reports of low back and leg pain intensity, quality of life, global rating of improvement, additional healthcare utilization, and work absence. Statistical analysis will be based on intention to treat principles and will use linear mixed model analysis to compare treatment groups, and examine the interaction between treatment and sub-grouping status.

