### Preliminary Research to Identify a Sub-Group of Patients Likely to Benefit from Traction

As an initial step towards investigating if a more clinically-relevant traction protocol would result in larger treatment effects, and to explore if a specific sub-group of patients with LBP exists for whom evidence would support the use of traction, we conducted a randomized clinical trial [29]. The inclusion criteria for this trial were designed to provide a more homogeneous sample that reflected clinicians' perceptions of the appropriate sub-group of patients most likely to benefit from traction. The trial required patients to have symptoms distal to the buttock accompanied by clinical signs of nerve root irritation. Because we hypothesized that clinically important heterogeneity may exist even within this more narrowly-defined sample of patients, we secondarily examined additional baseline variables, nominated based on expert opinion and observations, for their potential to further define a traction sub-group. The trial randomized patients to one of two treatment groups, both of which received 6 weeks of treatment involving an extension-oriented treatment approach (EOTA) comprised of repeated end-range extension exercises and supplemented with manual therapy and education designed to facilitate centralization of the patient's symptoms. One group also received mechanical traction during the first two weeks of treatment, in addition to this extension-oriented approach (EOTA+traction). The traction protocol was designed to reflect common clinical practice [28] and was informed by expert clinical input [30]. The protocol used a high dosage of traction, with a sustained traction force ranging between 40%-60% of a patient's body weight, delivered for a maximum of 12 minutes during a treatment session. The delivery of traction was combined with concomitant use of the EOTA interventions designed to enhance centralization of symptoms. We provided this high-dose traction during the initial 2 weeks of traction to reflect the clinical perception that traction is most effective when delivered early in the course of treatment, followed by transition to exercise or other patient-directed activities [30].

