## Methods/Design

### Overview of research design

The study will be a randomized controlled trial comparing an extension-oriented treatment approach (EOTA) with or without the addition of mechanical traction. The study will include patients with signs and symptoms consistent with lumbar nerve root irritation. Randomization will be stratified based on the preliminary sub-grouping criteria (table 1). The study design and subject flow are outlined in figure 3. Subjects in each treatment group will receive 12 individual treatment sessions with a physical therapist delivered over a 6-week period. Patients randomized to the traction group will receive traction combined with the EOTA throughout the 6-week treatment period. Outcomes will be assessed at the conclusion of treatment (6 weeks), and after 6 months and 1 year. The study has been approved by the Institutional Review Boards at the University of Utah, Intermountain Healthcare, Inc., and Wilford Hall Medical Center.

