#### Extension-Oriented Treatment Approach (EOTA) Group

The EOTA intervention involves three components. The goals of each component are to promote centralization of symptoms and extension range of motion of the lumbar spine. The first component will be a series of active extension-oriented exercises (table 3). These exercises will consist of sustained and repeated extension movements performed with the subject prone or standing. The exercises may be performed with a lateral component (i.e., shifting of the pelvis in the frontal plane) if this facilitates centralization. Exercises will be progressed at the treating physical therapist's discretion, guided by the principles of maximizing centralization of symptoms and increasing extension range of motion. Not all exercises will be used for every subject, only those which promote centralization or extension range of motion. Exercise progression will be accomplished by increasing the exercise time (up to 5 minutes for sustained exercises) or repetitions (up to 30 repetitions per session), increasing the range of motion towards greater lumbar extension, and adding over-pressure once the end-range of extension range of motion is obtained. Subjects will be instructed to perform all assigned exercise activities at home, every 4-5 hours throughout the day, on days when they do not have a treatment session. Subjects will be provided a copy of an exercise instruction booklet with detailed written descriptions and pictures of the proper performance, frequency, and progression of each exercise. Subject compliance with their home exercise program will be recorded by the treating physical therapist at each treatment session.

**Table 3 T3:** Exercise progression within the extension-oriented treatment approach.

Extension-Oriented Exercises	Goal	Options for Progression
Prone Lying	5 minutes	May use pillow to allow lumbar flexion initially if needed May shift pelvis laterally if needed Progress to full lumbar extension without pillows or lateral shift of pelvis Progress time up to 5 minutes

Prone Lying on Elbows	5 minutes	May use partial range of extension motion initially if needed May shift pelvis laterally if needed Progress to full lumbar extension with-out lateral shift of pelvis Progress time up to 5 minutes

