Prone Press-Ups	30 repetitions	May use partial range of extension motion initially if needed May shift pelvis laterally if needed Progress to full lumbar extension with-out lateral shift of pelvis Progress to exhalation during the last repetition to promote increased extension Progress to therapist over-pressure during repetitions to promote increased extension Progress up to 30 repetitions

Extension in Standing	30 repetitions	May use partial range of extension motion initially if needed May shift pelvis laterally if needed Progress to full lumbar extension with-out lateral shift of pelvis Progress up to 30 repetitions

The second component of the EOTA will be subject education. Subjects will be educated to maintain the natural lordosis of the lumbar spine while sitting, and will be instructed to avoid prolonged sitting for greater than 20-30 minutes whenever possible. Additionally, subjects will be educated on the principles of symptom centralization/peripheralization, and will be given general instructions to discontinue any activities and avoid positions that cause symptoms to peripheralize, and to encourage activities or spinal positions that centralize or improve symptoms.

The third component of the EOTA will be mobilization of the lumbar spine to promote lumbar extension. The mobilization component will consist of a series of up to 20 graded oscillatory mobilizations performed with the subject prone. The physical therapist will apply a posterior-to-anterior mobilization force directed over the spinous process, or laterally over the transverse process, using a grade I - IV mobilization force as described by Maitland [42]. The therapist will select the specific grade(s) and spinal level(s) for mobilization during each treatment session based on the consideration of promoting centralization and lumbar extension range of motion.

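### Mobilization is deferred to week 3 in the EOTA + traction arm with no such delay stated for the EOTA arm, so H1, H2 and H3b compare two packages, not traction added to an otherwise identical EOTA

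*Protocol article*

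**What the plan says.** All places are in the protocol article.

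- *Extension-Oriented Treatment Approach (EOTA) Group*: "The EOTA intervention involves three components". These are exercise, education and mobilization. On the last: "The third component of the EOTA will be mobilization of the lumbar spine to promote lumbar extension". On its delivery: "The therapist will select the specific grade(s) and spinal level(s) for mobilization during each treatment session". This section gives no delayed start. The number of oscillations has an upper limit of 20 and no lower limit.
- *EOTA + Traction Group*: the section opens by saying that the EOTA components apply in this arm too, and closes with the exception: "The mobilization component of the EOTA will be added in the 3^rd ^week for patients in the EOTA plus traction group". For exercise the two arms are matched where the patient can tolerate it: "the subject will be instructed to perform the same home program of extension-oriented exercises as described in the EOTA group".
- *Overview of research design*: "Patients randomized to the traction group will receive traction combined with the EOTA throughout the 6-week treatment period".
- *Interventions*: 12 sessions over 6 weeks in both arms, with three sessions in weeks 1 and 2, two in weeks 3 and 4, and one in weeks 5 and 6.
- Abstract, *Methods/Design*: "Patients will be randomized to receive an extension-oriented treatment approach, with or without the addition of mechanical traction". *Hypotheses*, *Data Analysis* and *Discussion* frame the question in the same way, as the effect of adding traction to EOTA. None of them mentions the later start of mobilization, and no section gives a reason for it.

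**The concern.** An add-on trial answers the question of what the added treatment does when everything else is the same in both arms. Here the background treatment is not fully the same. During the first two weeks the traction arm gains traction and goes without one of the three EOTA components, while the comparator arm may receive that component.

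Randomization protects the comparison of the two regimens as delivered. It cannot separate the two differences from each other, because they are assigned together. If the trial reports the between-arm difference as the effect of adding traction, part of that difference may belong to the later start of mobilization. A clinician who adds traction to a full EOTA that includes mobilization from the start would be using a regimen that the trial did not test. A null result has the same ambiguity.

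**Working it through.** **1. When week 3 begins.** Input: the schedule in *Interventions*. Read as sessions per week it gives 3 + 3 + 2 + 2 + 1 + 1 = 12, which reproduces the stated total of 12. Read as totals per two-week period it gives 3 + 2 + 1 = 6, which does not. The per-week reading therefore holds.

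- Sessions in weeks 1 and 2: 3 + 3 = 6.
- First session of week 3: 6 + 1 = session 7.

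**2. Sessions in which mobilization is available.**

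| Arm | First available session | Basis | Sessions available |
|---|---|---|---|
| EOTA + traction | 7 | stated (week 3) | 12 − 6 = 6 of 12 |
| EOTA | 1 | inferred: no delay stated | 12 of 12 |

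The inference for the EOTA arm has two supports. Grade and level are chosen at each session, and the week 3 rule is written for the traction arm alone, which would be unnecessary if both arms started then. It is still an inference.

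**3. Range of the difference.** Mobilization is at the therapist's discretion and has no minimum. The number of sessions that can differ per patient therefore runs from 0 (EOTA-arm therapist does not mobilize in weeks 1 and 2) to 6 (mobilizes in every one of those sessions), that is 0/12 = 0% to 6/12 = 50%.

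**4. What each contrast estimates.** Let T be the effect of traction and M the effect of having mobilization in weeks 1 and 2, both on the outcome at a given follow-up and both signed so that positive means benefit. Assume for illustration that they add. Superscripts + and − mark patients who meet or do not meet the sub-grouping criteria.

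- H1 and H2 (arm against arm): T − M.
- H3b (criteria-positive patients, arm against arm): T⁺ − M⁺.
- H3a (positive against negative within the traction arm): both groups have the same mobilization schedule, so the deferral does not differ between them.
- Treatment by sub-group interaction: (T⁺ − M⁺) − (T⁻ − M⁻) = (T⁺ − T⁻) − (M⁺ − M⁻). The deferral drops out unless early mobilization works differently in the two sub-groups.

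If M > 0, the contrast understates T. If M < 0, for example because early mobilization aggravates irritated roots, it overstates T. If M = 0, they agree. The documents give no value or sign for M.

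**5. Sample size.** The calculation uses an effect size of 0.50, a baseline correlation of 0.57, an inflation of 1.2 and a drop-out of about 13%: 128 × (1 − 0.57²) = 86.4, 86.4 × 1.2 = 103.7 (stated 104), and 104 / (1 − 0.13) = 119.5, giving 120. Rewording the contrast changes none of these inputs.

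**The case against.** The strongest reply is that this is a comparison of two defined protocols and that the deferral is a written, disclosed rule of one of them. The hypotheses compare treatment groups, no sentence claims that a difference would be due to traction alone, and adding traction is ordinary shorthand. In addition, the dose of mobilization is discretionary, so the real difference could be nil. By the first outcome assessment at 6 weeks, traction-arm patients have had access to all three components for four weeks.

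Much of this stands. Disclosure is real, and the actual difference may be small. What remains is that the sections stating the question and the intended conclusion name only traction, so a reader of the result would not learn from them that the background treatment also differed.

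Several stronger readings are tempting, and the documents do not support them:

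- *The protocol contradicts itself.* The rule in *EOTA + Traction Group* is a specific one that qualifies the general statements elsewhere. The sentence in the *Overview* about the full six weeks can be read as the duration of traction.
- *Only the traction arm receives mobilization.* Both arms have it. Only the later start is specific to the traction arm.
- *The traction effect is biased in a known direction, or power is lost.* Any such figure needs an assumed effect of early mobilization, and the documents give none.
- *The deferral falls in the critical period for traction.* The Background does report a perception that "traction is most effective when delivered early in the course of treatment", but this explains why the preliminary trial gave traction for two weeks only. The present trial gives it for six weeks and has no 2-week outcome.

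**Conclusion.** The point holds as a mismatch between the treatments given and the effect named. H1, H2 and H3b estimate the effect of EOTA plus traction with mobilization deferred to week 3, against EOTA with no such deferral. They do not isolate traction added to an otherwise identical EOTA, which is how *Hypotheses*, *Data Analysis* and *Discussion* describe the contrast.

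The deferral itself is certain for the traction arm (session 7 of 12). The difference between arms, 0 to 6 of 12 sessions per patient, rests on the inference that EOTA-arm patients may be mobilized from session 1. The consequence for the outcome has unknown size and direction. It would be wrong to infer that the trial is invalid: the randomized comparison of the two regimens stands, as do the sample size of 120, the mixed-model analysis and H3a. The three-way interaction is touched only if early mobilization acts differently by sub-group.

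**What to change.** In *Hypotheses*, *Data Analysis* and *Discussion*, restate H1, H2, H3b and the planned conclusion as EOTA plus traction with mobilization deferred to week 3 versus EOTA with no such deferral, and interpret the result as a comparison of packages. H3a needs no change.

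This is wording only. It alters no treatment, visit, patient number or model. The downside is a slightly narrower claim.

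Two further steps are optional. The deferral could be repeated in *Overview of research design*, in *Interventions* and at the start of *EOTA + Traction Group*. Mobilization received could be tabulated by arm and session from the session forms described in *Physical Therapist Training and Compliance*, which would show where in the range of 0 to 6 sessions the actual difference lies. Giving mobilization the same start in both arms would remove the issue, but that is a clinical decision for the investigators and is not required.

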#### Treatment Side Effects

A questionnaire for reporting any side effects the subject perceives to be related to treatment procedures will be completed by the subject at the 6-week follow-up. The questionnaire is based on a questionnaire used previously to examine subjects with LBP receiving spinal manipulation [43]. Subjects are asked if they experienced any commonly-reported side effects following treatment including stiffness, muscle spasm, fatigue, or increased radiating symptoms. Subjects will also be able to report side effects not specifically named. For each side effect reported, the subject is asked to report the time of onset relative to the precipitating treatment session (≤24 hours or >24 hours), the duration of the side effect symptoms (≤24 hours or >24 hours), and severity of symptoms (categorized from 1 "light" to 4 "severe").

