II. Sensory deficit to pinprick on the ipsilateral lower extremity	**7**. Known inability to comply with the treatment schedule (e.g., planned vacation, etc.)
III. Diminished myotomal strength of the ipsilateral lower extremity	
IV. Diminished lower extremity muscle stretch reflex (Quadriceps or Achilles) of the symptomatic lower extremity	

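### The only side-effect measure described records what the unblinded patient attributes to treatment, so any comparison between arms is open to differential attribution of unknown size and direction

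*Protocol article*

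**What the plan says.** The Treatment Side Effects section describes a single instrument, completed at the 6-week follow-up: "A questionnaire for reporting any side effects the subject perceives to be related to treatment procedures will be completed by the subject". It is "based on a questionnaire used previously to examine subjects with LBP receiving spinal manipulation". Patients are asked about "commonly-reported side effects following treatment including stiffness, muscle spasm, fatigue, or increased radiating symptoms", and there is an open item: "Subjects will also be able to report side effects not specifically named". For each effect reported, "the subject is asked to report the time of onset relative to the precipitating treatment session", together with duration and severity.

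Other sections bear on how this works:

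- **Interventions.** One arm receives the extension-oriented approach (EOTA) alone, and the other receives it with motorised traction. No sham traction is described.
- **Table 2.** The signs that can qualify a patient for entry include a sensory deficit and "Diminished myotomal strength of the ipsilateral lower extremity".
- **Outcome Measures.** Oswestry disability, back and leg pain, global rating of change and EQ-5D are collected at follow-up. Monthly contacts for a year cover healthcare use and work absence due to back pain. No repeat test of strength or sensation is listed.
- **Hypotheses and Data Analysis.** Neither states a comparison of side effects between arms.

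**The concern.** The point is what is counted, not when it is asked. If a symptom is recorded as a side effect only when the patient believes treatment caused it, the reported rate combines two things: how often the symptom occurs and how readily patients blame treatment. Randomisation balances the first under the null. It does not balance the second, because patients know which treatment they are having.

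Two things are at stake. A table of side effects by arm could show an excess, or hide one, because of attribution alone. Neurological worsening that a patient ascribes to the back condition could also go unrecorded as a side effect in either arm. The second matters here because motor and sensory deficits are among the signs that bring patients into the trial, so their worsening is foreseeable.

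**Working it through.** The document gives no side-effect rate and no harms hypothesis, so there is no stated figure to reproduce. The check compares the relevant sections and then uses assumed rates to show how the mechanism behaves.

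**1. Is recording tied to perceived cause?** Yes, as described. The sentence that introduces the questionnaire limits it to effects perceived as related to treatment procedures. The item description is looser: it speaks of effects following treatment, which is partly about timing.

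**2. Can attribution differ by arm?** Yes. Without a sham, patients know whether they receive a pull of 40-60% of body weight. The control arm also has hands-on treatment to which symptoms could be attributed: mobilization (grades I-IV) and therapist over-pressure. In the traction arm, mobilization is added only in the third week. The direction is therefore not evident.

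**3. Are weakness and numbness named?** The article names four items: stiffness, muscle spasm, fatigue and increased radiating symptoms. Neither weakness nor numbness is among them. The wording that introduces the four allows them to be examples, and the open item exists.

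**4. Do other measures fill the gap?** In part. Leg pain, Oswestry, global change and the monthly utilization contacts do not depend on attribution. None measures strength or sensation.

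**5. Size, with assumed rates.** Let p be the true risk, equal in both arms, and let a_T and a_C be the proportions of affected patients who attribute the event to treatment.

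Reported rates are p × a_T and p × a_C, so the apparent risk ratio is a_T / a_C, whatever p is.

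| p | a_T | a_C | Reported rates | Difference | Ratio |
|---|---|---|---|---|---|
| 30% | 80% | 50% | 24% vs 15% | +9 points | 1.60 |
| 30% | 60% | 50% | 18% vs 15% | +3 points | 1.20 |
| 40% | 90% | 70% | 36% vs 28% | +8 points | 1.29 |
| 40% | 90% | 50% | 36% vs 20% | +16 points | 1.80 |
| 20% | 90% | 50% | 18% vs 10% | +8 points | 1.80 |
| 40% | 50% | 90% | 20% vs 36% | −16 points | 0.56 |

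Equal attribution gives a ratio of 1. With 60 per arm and a 5% test (taken as two-sided, since the article does not say), 36% against 20% would be declared different in about 50% of trials, and 18% against 10% in about 24%, although the true risks are equal.

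**6. Missed events, with assumed rates.** If a fraction q of patients in an arm of 60 worsens neurologically and a fraction c of those cases is recorded, the chance that the arm shows no case is (1 − qc)^60.

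- q = 2%: 0.98^60 = 30% with full capture, and 0.99^60 = 55% with half captured.
- q = 5%: 0.95^60 = 5% with full capture, and 0.975^60 = 22% with half captured.

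**The case against.** The strongest reply is that the article is a condensed account and the form itself is not shown. The phrase about perceived relatedness may be a summary rather than the question put to patients. The full protocol may contain separate adverse-event reporting, and the analysis plan may define how harms are compared. This limits how far the point can go. It does not change how the one measure that is described is framed.

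A reader might draw stronger conclusions that the document does not support:

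- *The harms comparison is biased against traction.* No attribution rates are given. EOTA patients receive mobilization and over-pressure, and education in both arms teaches patients to link activities and positions to their symptoms. Bias could run either way or be absent, and no harms comparison is stated.
- *The form leaves out neurological harm.* The four named items may be only examples, increased radiating symptoms may pick up part of the worsening, and the open item allows anything else to be written in. Weakness and numbness are not prompted by name in the article. That is different from being excluded.
- *An event counts only if it can be tied to a session.* The onset question describes an effect already reported. Nothing says that a report without it is dropped.
- *A patient who blames the disc leaves no trace of worsening.* Leg pain, Oswestry, global change and monthly utilization are collected whatever the patient believes.
- *A form derived from manipulation research is unsuitable.* Its origin is not a fault in itself; what matters is its content.

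**Conclusion.** The point holds in limited form. The only side-effect measure described is framed by the unblinded patient's judgement of cause, so a comparison between arms is open to differential attribution. The document does not show that such bias will occur, and its size and direction cannot be determined from it. The ratios of 0.56 to 1.80 above show what the assumed attribution rates would produce; they are not estimates for this trial.

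The neurological part is narrower. New or worse weakness or numbness is not among the items the article names, so its capture as a side effect may rest on the open item, and the other outcomes show it only indirectly.

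This is a design choice with a better and cheap alternative, not an error or a contradiction. It does not affect the primary Oswestry analysis or the sample size. It rests on two assumptions: that the form follows the article's description, and that no separate adverse-event record, free of perceived cause, exists in the full protocol.

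**What to change.** Check the form first. If it reads as the article describes:

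1. Ask about any new or worsened symptom since treatment began, whatever the patient believes caused it.
2. Name new or worse leg weakness, new or worse numbness, and change in bladder or bowel control among the items, if they are not already there.
3. Keep perceived relatedness to treatment as a separate item, so that the attributed data are not lost.
4. Report all events by arm, with perceived-related events as a secondary listing.

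The cost is rewording one existing form and adding up to three symptom lines and the relatedness item. More events will be reported, some of them natural course. Randomisation should make that background comparable between arms. Patients remain unblinded, so differences in willingness to report can persist, but the causal judgement no longer decides what is recorded.
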